### 6. Primary and secondary outcome measures

**Primary Outcome measures:** Asthma control, health care utilization, pulmonary function and asthma-relate quality of life. The main aim of the intervention is to improve asthma control and improve quality of care for asthma, in keeping with the 2007 NAEPP Guidelines 29. The NAEPP guidelines state that the goals include “minimal or no chronic symptoms day or night” and “no limitations on activities” 29. We hypothesize that each of these measures will be improved in the IC, compared to the CC.

Asthma Control: We will measure asthma control using the Asthma Control Test (ACT), at baseline, 6 months, and 12 months. The ACT asks patients about several aspects of their asthma control over the past 4 weeks: a) whether their asthma interfered with their activities, b) how often they had shortness of breath from asthma, c) how often they used their rescue inhaler, d) how often they had asthma symptoms at night and e) an overall impression of their asthma control. The ACT has a test-retest reliability of 0.84 and compares closely with a specialist’s rating of asthma control, the need for change in patient’s therapy and percent predicted FEV1, future asthma control and future emergency department visits 98-100. The ACT is also sensitive to changes in asthma treatment 99. The overall agreement between ACT and the specialist’s rating ranged from 71% to 78% depending on the cut points used, and the area under the receiver operating characteristic curve was 0.77 98. An ACT score of ≥ 20 will be used as a cutoff for determining “controlled” v. “uncontrolled” asthma, as this cutoff demonstrated the highest area under the ROC curve. The use of the ACT, as well as the cutoff of 20 for determining control are supported in the 2007 NAEPP Guidelines on page 345 26. We hypothesize that, at 12 months, 70% of subjects in the IC condition will have an ACT of ≥ 20 versus only 55% in the CC condition.

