Asthma-Related Emergency Department Visits: Improvements in asthma control can decrease future use asthma-related emergency room visits, so we will measure asthma-related emergency department visits 6,100,101. Claims data are valid measures, and superior to other means, such as self-report, for measuring asthma-related emergency department visits. 102,103. Highmark will send us claims data, at the end of the study, which will identify asthma-related emergency department claims. This is data that is already being analyzed by Highmark, in ways that are standardized by the National Committee for Quality Assurance (NCQA), for reporting the quality of care delivered to patients with asthma 7. In the NCQA reporting, asthma-related emergency department visits are one way to identify patients with persistent asthma 7. We will take advantage of that reporting mechanism in the current study.

Asthma Control and Quality of Life: We will use questions about asthma control and quality of life from the National Asthma Survey, from the CDC and published by Halterman and colleagues (Halterman, Aligne et al. 2000). The instrument identifies several aspects of asthma control and how it impacts quality of life, including days with symptoms, days symptom-free, emergency room visits, urgent doctor visits, asthma attacks, severity of asthma attacks and the degree to which asthma impairs function. It is not clear how many of these questions are validated, but they are used as outcome studies in a great number of asthma clinical trials and have strong face validity and national norms is helpful. Drs. [name], [name] and [name] are working on the adult version of the Halterman paper, using the data from the NAS.

**Mediating Variables:** For our purposes, mediating variables are those that the intervention will attempt to modify in order to bring about a change in asthma control and quality of care for asthma. We will examine variables that have been associated with asthma control and quality of care for asthma and those that have been targeted by the intervention and therefore may mediate the effect of the intervention on the above outcome variables. We hypothesize that each of these variables will mediate the effect of the intervention.

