Controller to reliever ratio: There are generally two types of medicines for asthma; those used for quick relief of asthma symptoms (“relievers”), and those that are used daily to prevent asthma symptoms (“controllers”). Using a controller medication is the first step in managing persistent asthma, according to the treatment algorithm (page 343) on the 2007 NAEPP Guidelines 26, and has served as a main outcome measure in many quality improvement studies 66-68,104. By using more controller medicines, therefore, the number of reliever medicines tends to go down 105. The ratio of controller/reliever canisters is strongly predictive of future emergency department visits and, as such, has been used as a measure of asthma control and quality of care 105-107. As the intervention is designed to help individuals receive a controller medicine and, for those whose asthma is not controlled, often a second controller medicine, the controller to reliever ratio should be sensitive measure of the effects of the intervention. We will use standard ways to express this variable, which will be calculated as the ratio of the number of controller medications (i.e., inhaled corticosteroid) dispensed during the study year divided by the sum of the number of controller medications dispensed plus the number of canisters of inhaled relievers (e.g., short-acting beta-2-agonists) dispensed during the study year. This ratio ranges from 0 (no controller medications) to 1.0 (no reliever medications) 105-108. Grymonpre and colleagues observed that the concordance between claims data on medication acquisition and pill counts was between 79% and 88%, which were both highly significant 109. This data will be captured in the electronic claims data from Highmark, as none of the medicines are inexpensive, so patients should find it less expensive to use their prescription drug coverage through Highmark than to pay out of pocket. Similar methods are used by the National Committee for Quality Assurance to estimate the quality of asthma care in over 500 health plans nationally 7.

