### 7. Statistics and sample size justification

Sample size considerations focus on the primary hypothesis posited in the Specific Aims section. The major research goal is to determine the efficacy of having patients use the asthma module of the interactive website, for a period of 12 months, for improving asthma control. The primary outcome will be asthma control, based on the Asthma Control Test (ACT), a valid and reliable 5-question self-report measure of asthma control. 98-100. We chose to power the study based on asthma control, as it is a powerful predictor of emergency department visits, activity limitations and missing days of work due to asthma 6,100,130, and it is a central goal in both Healthy People 2010 as well as in the 2007 NAEPP Guidelines 26,131. We chose not to power the study on improving the use of controller medications, such as inhaled corticosteroid use, as the rates of use of these medications has increased greatly over the past decade, which would lead to a ceiling effect 7. Despite the broad use of these controller medications, however, asthma control rates are still in the 50% range, so we will not suffer from such a ceiling effect 5. Our estimated baseline rate of 55% is based on two studies of asthma control in similar groups of insured patients that both showed asthma control rates in the 50% range 5,6. For example, Schatz and colleagues observed that 48.4% of 570 insured adults with asthma had an Asthma Control Test (ACT) score of less than 20, the same measure of asthma control that we are using in the current study 5. Vollmer and colleagues reported that 48% of 5,181 insured adults with asthma reported good asthma control, using a slightly different measure of asthma control, the Asthma Quality of Life Questionnaire 6. We expect a slightly higher baseline control rate, as patients who volunteer for clinical trials tend to be healthier than those who do not 132. This expected effect size is based on a meta-analysis by Stone and colleagues that examined the efficacy of reminders, given to patients, on rates of adult immunization and cancer screening services 16. Patient reminders, similar to what we plan to use in the current study, significantly increased immunizations (odds ratio, OR=2.5), mammography utilization (OR=2.3), cervical cytology screening (OR=1.7) and colon cancer screening (OR=2.8). These effect sizes are consistent with reviews by other investigators 23,50,133. In the current study, we will be powered to detect an effect size that translates to a relative risk of 1.3 (0.70 /0.55) and odds ratio of 1.9. We chose this conservative effect size to address the fact that we are not examining a process of care but an outcome of care. While we expect the intervention to lead to increases in the number of controller medications used, additional medications do not always help patients. Also, we need to be sensitive to the possible differences in efficacy between interventions to increase adult preventive services (e.g., pap testing) and studies such as ours that seek to change chronic disease management practices. We considered powering on a numerical change in the Asthma Control Test (ACT), our main outcome measure, but chose not to do this as there is less consensus about what represents a meaningful change in the ACT than there is about what represents appropriate asthma control 5,98. We will, however, analyze changes in the ACT as a continuous variable, in our secondary analyses. Formulas based on the chi-square test were used to derive sample size calculations from the following assumptions. We assume a type I error rate (alpha) of 5% (0.05), 80% (0.80) power, and a two-tailed test, which allows us to detect significant differences in either direction. We expect a 12-month retention rate of 80%, although we believe that our procedures will substantially minimize the likelihood of attrition. We considered randomizing providers but felt that, given the number of providers in the two geographical areas, it was very unlikely that a physician would have more than one subject enrolled in the study. We will, however, track the name of the asthma care provider, so that we can include this variable in a sensitivity analysis, to be certain that adding this variable does not change the conclusions of the data analyses. In order to achieve 80% power to detect a difference of 70% vs. 55% between intervention and control group, we will need to randomize 408 patients into the two conditions at baseline. This assumes that no more than 20% are lost to follow-up at 12 months, leaving no fewer than 326 subjects available for analysis at the end of the study. We do concede, however, that smaller differences in asthma control may be clinically important, particularly on a population level. To power the study on a 10% difference in asthma control, however, we would have needed to recruit 940 subjects, which we felt would unnecessarily increase the cost and complexity of the study.

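### Testing the controller-to-reliever ratio as a mediator of the ACT effect is biased towards a positive finding, because reliever use sits in both the ratio and the ACT

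*Protocol*

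**What the plan says.** In Protocol section III.6, the Mediating Variables paragraph introduces a list of variables and states: "We hypothesize that each of these variables will mediate the effect of the intervention". The outcomes described above that list begin with asthma control on the ACT. The controller-to-reliever ratio is on the list. It is defined as controllers dispensed in the study year, divided by that number "plus the number of canisters of inhaled relievers" dispensed in the same year. The same paragraph says the ratio "has been used as a measure of asthma control and quality of care".

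The ACT, described earlier in III.6, covers the past 4 weeks. Its third item is "how often they used their rescue inhaler".

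Section III.7, under the mediating and moderating analyses, fixes the method: the four-step Baron and Kenny procedure, one mediator at a time. It also undertakes in general terms to look at the timing of events and measurement periods. The ratio appears as a secondary outcome too, in the Specific Aims and in the secondary analyses of III.7.

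**The concern.** A mediator should lie between treatment and outcome. Reliever use is largely a consequence of how well asthma is controlled, and the ACT counts it as part of control. With relievers in its denominator, the ratio carries a pharmacy-claims version of part of the outcome, accumulated over a period that runs up to the outcome's own recall window.

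The protocol itself expects control to improve by several routes. Besides controllers, it names counselling on early symptoms, environment change and action plans. If one of these works, reliever dispensing falls and the ratio rises even when no controller prescription changes. Because mediators are examined singly, no model separates that from a controller effect. A reader could then conclude that the website works by changing controller treatment when the data show only that better-controlled patients collect fewer relievers.

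**Working it through.** **The protocol's own figure.** Section III.7 says "we will need to randomize 408 patients into the two conditions at baseline" in order "to detect a difference of 70% vs. 55% between intervention and control group". Inputs are two-sided alpha 0.05, 80% power and 20% loss. With the pooled chi-square formula and no continuity correction:

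- n per arm = [1.960·√(2·0.625·0.375) + 0.8416·√(0.55·0.45 + 0.70·0.30)]² / 0.15² = (1.3419 + 0.5693)² / 0.0225 = 162.3, rounded up to 163.
- Total 2·163 = 326, and 326/0.80 = 407.5, rounded up to 408. Power at 163 per arm is 80.2%.

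The figure reproduces. The mediation question does not touch it.

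**How the ratio moves without any controller change.** The dispensing rates here are assumptions; the protocol gives none. Take 6 controllers and 4 relievers a year, so the ratio is 6/(6+4) = 0.60. Suppose treatment lowers symptom burden by 0.45 SD, and relievers follow burden with log-slope 0.4. Relievers become 4·exp(−0.4·0.45) = 3.34 and the ratio becomes 6/9.34 = 0.64. At slope 0.8, relievers become 2.79 and the ratio 6/8.79 = 0.68.

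**Simulation of the four steps.** There were 326 patients and 800 trials per setting. Assumptions:

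- Symptom burden is standard normal, shifted by −0.45 in the intervention arm, with noise and a cut-off set so that control rates are about 55% and 70%.
- Controllers are Poisson with mean 6, unaffected by treatment and unrelated to outcome.
- Relievers are Poisson with mean 4·exp(slope × burden).

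True mediation through controllers is therefore zero. Step (d) was taken first as any fall in the treatment coefficient (column *All four*). The stricter column requires step (a) plus a significant indirect effect.

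| Slope | Treatment→ratio significant | Ratio→ACT significant | All four | Stricter | Apparent share mediated |
|---|---|---|---|---|---|
| 0 | 4% | 5% | 0% | 0% | 0% |
| 0.2 | 20.5% | 93.5% | 17% | 8% | 8% |
| 0.4 | 51% | 100% | 44% | 41% | 24% |
| 0.6 | 73% | 100% | 63% | 62% | 41% |
| 0.8 | 83% | 100% | 71% | 71% | 55% |

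The share is 1 minus the treatment coefficient with the ratio divided by the coefficient without it, from linear probability models. At slope 0.8 this is 1 − 0.070/0.154, or about 55%. A controller-only count in the same trials passed in at most 0.5%. With no treatment effect on the ACT (slopes 0.2 and 0.6), the ratio passed in 0%.

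The ratio-to-ACT step is thus close to automatic once relievers follow symptoms at all. What limits the false finding is the treatment-to-ratio step and the need for an ACT effect.

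**The case against.** A reader might infer that a false mediation finding is guaranteed by the way the ratio is built. The protocol does not support that. Step (a) requires a treatment effect on the ACT, and without one the simulated rate was 0%; it was also 0% when relievers did not follow symptoms. The overlap is partial: one self-reported item of five over 4 weeks, against claims over a year.

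The simulation also leans towards a large bias. One constant level of control drives both the year's relievers and the 12-month ACT, whereas real effects would probably build up over provider visits. It sets controller change to zero although the intervention is meant to increase controllers, so part of any real movement in the ratio could be true mediation. The controller-only rate is low by assumption; it locates the bias in the reliever term and does not prove the replacement sound. All of this stands, and it limits the claim to a bias of unknown size.

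Two further arguments carry less weight. Medication possession ratio is already a listed controller-only mediator, but it measures adherence, which the protocol says is not the intervention's main focus, and does not directly capture the addition of a controller. The undertaking to consider timing is general, and a single whole-year ratio cannot be placed before a recall window inside that year. Nor does step (a) help where it matters, since mediation is of interest only when there is an ACT effect.

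A reader might also infer that the ratio should be dropped as a mediator of every outcome. That goes too far: the shared item is in the ACT, not in claims-based emergency department visits.

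**Conclusion.** The concern holds as a bias, not as a certainty. When the intervention improves the ACT by a non-controller route, the planned analysis leans towards showing mediation by the ratio. If the whole effect is non-medication, the illustrative four-step false-finding rate is about 17% to 71% at assumed log-slopes of 0.2 to 0.8 (8% to 71% under the stricter criterion). These figures rest on assumed dispensing rates and slopes; the protocol supplies neither, so they show a range and do not predict this trial. The role, definition, window and method are all stated in the protocol, so this is not a detail left to a later analysis plan. It affects the interpretation of one mediator in a non-primary analysis; the primary comparison and the 408 patients stand.

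**What to change.** Keep the ratio as a secondary outcome. In III.6 and the mediation paragraph of III.7:

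- For mediation of the ACT, name a controller-only measure from the same claims as the medication-pathway mediator: controller days' supply, or any controller addition. Count it from randomisation to the start of the 12-month ACT recall window, and adjust for baseline ACT.
- State that mediation of the ACT by the ratio will not be read as evidence of a controller pathway. If it is reported, repeat it with the ratio restricted to the pre-recall period, and again with an ACT score that omits the rescue-inhaler item. Analyse that shortened score as continuous, because the cut-off of 20 belongs to the five-item test.

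The cost is a short edit and a little more analysis; the claims extract is already planned and no new data are needed. One limitation should be written in: controller additions may be prompted by poor control, so the controller-only result may understate mediation. Adjustment for baseline ACT reduces this only in part.

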Overall, the control condition is an active treatment control condition, in which subjects will be treated identically, except that the content of the questions and feedback on the interactive website will focus on adult preventive services (e.g., mammography screening, tetanus immunizations) rather than asthma. The control condition is an active treatment control condition designed to improve the use of adult preventive services (e.g., pap testing), but is unlikely to change asthma care. This control condition design was chosen to limit attrition and control for contact time, which will best enable us to isolate the effects of the intervention. Many similar studies have used this control group design 91-93. We considered several different control conditions, including a no treatment control condition and a delayed treatment control condition. As patients with chronic medical conditions, such as asthma, are less likely to receive preventive services such as pap testing and mammography 94-96, we have chosen an active treatment control condition that seeks to meet a need of patients with asthma, but will not interfere with our main research questions. In addition, Halpern and colleagues noted that subject recruitment and retention is enhanced in studies in which the control group receives an “active” intervention, rather than a placebo intervention 97. The control condition is identical to the control condition currently being used in the study to test the effect of the intervention for hypertension control.

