### 5. Procedures to be followed

Potentially interested participants will call a toll-free number and speak to a study coordinator, who will complete a phone screener. The phone screener includes questions in the following categories: basic demographic information, race and ethnicity, exclusion criteria questions, contact information (e.g., phone number) and social security information, so that we are able to mail compensation for participation in the study. Data from this phone screening process will be collected on paper and parts of this form will be later entered into the management module. During this phone screener, the study coordinator will explain the study, ask questions to determine eligibility and then ask once again if the patient may be interested in participating. If the participant is eligible and interested, the study coordinator will read the verbal consent document over the phone. If the participant is interested, eligible and consents to participate in the study over the phone, the study coordinator will inform the participant that he/she is included in the study and will receive an email within the next day from the study, explaining what will happen next. The coordinator will also inform the participant that upon logging into the application for the first time, they will have to read, review, and electronically agree to a Member Authorization Form by Highmark. They will be able to print out this form for their own records. Those that do not agree will not be allowed to participate. Those that do agree will then be randomized automatically, according to an algorithm written in the management module, to either the asthma or preventive care modules. The study coordinator will enter the specific screening information into the application (all screening fields except for mailing address and SSN) after their phone call with the participant and then check a box representing that the participant has completed the phone consent procedure. The participant will then be asked to use the website once every 30 day cycle and within 14 days of their next scheduled visit with their asthma care provider. At baseline, 6 months, and 12 months, they will be asked to complete specific measures online, as outlined below. During other monthly logins, they will be asked to complete short surveys that will then generate feedback based on their group they were randomized to. Women of child bearing potential will be asked monthly if they are currently pregnant and if they state that they are, they will be withdrawn from the study. At the close of the study, Penn State researchers will be authorized to provide Highmark with the names, DOB’s, gender and dates participants electronically agreed to the Member Authorization Form. Highmark will then provide Penn State researchers with access to claims data for all enrolled participants, for the 2 years prior to study participation and up to 2 years post enrollment. Asthma-related claims of hospitalization, outpatient visits, emergency department visits and medications will be examined.

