
|  | Phone Screener | Base | Every 30 days | CYCLE 6 | CYCLE 13 | Claims |
| --- | --- | --- | --- | --- | --- | --- |
| Age, gender, race, ethnicity (5) | X |  |  |  |  |  |
| Exclusion (smoking amount, Internet access, asthma history, English fluency)(10) | X |  |  |  |  |  |
| Contact and payment information (13) | X |  |  |  |  |  |
| Demographics, height, weight, QOL (14) |  | X |  |  | X |  |
| Asthma Control Test (5) |  | X |  | X | X |  |
| Asthma Control and Quality of Life (11) |  | X |  | X | X |  |
| Health Conditions (14) |  | X |  |  |  |  |
| Patient Satisfaction Questionnaire (19) |  | X |  |  | X |  |
| Patient Involvement (5) |  | X |  |  | X |  |
| Health Literacy (2) |  | X |  |  | X |  |
| Internet Use (29) |  | X |  |  | X |  |
| Asthma Counseling (5) |  | X |  |  | X |  |
| Newest Vital Sign (8) |  | X |  |  |  |  |
| CC Condition Pre-Use Questions (27) |  | X | X* |  | X |  |
| IC Condition Pre-Use Questions (16) |  | X | X* |  | X |  |
| Emergency department visits |  |  |  |  |  | X |
| Medication use and adherence |  |  |  |  |  | x |
| Outpatient provider visits for asthma |  |  |  |  |  | X |
| Adverse events |  |  |  | X | X |  |
| Satisfaction with Intervention |  |  |  |  | X |  |
| Pregnancy Question | X** | X** | X** | X** | X** |  |

* depending on condition randomized to, each subject will complete either the CC or IC questions

** asked to women of child bearing potential only

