Intervention fidelity: Use of interactive website before asthma care provider visits. Use of the interactive website will be tracked passively. Each login by study subjects will be recorded, as will the duration of each login, the number of pages viewed, any data entered and the number of times that subjects received the computer-tailored feedback. The active part of the intervention is felt to be the computer-tailored feedback, so this measure will represent the “dose” of the intervention. Dose will be measured as a proportion of asthma provider visits before which the website was used, expressed as a percentage. The number of visits with an asthma care provider will be obtained from chart review, and will be the denominator for this measure. The number of visits that subjects used the website within two weeks prior to these visits will be the numerator for this measure. We consider visits to an asthma care provider to be any visits to the patients’ primary care provider as well as any visits that the patient had with a pulmonary medicine specialist during the study. Upcoming visit dates will be tracked using brief monthly emailed surveys to patients. These surveys will seek to clarify the date(s) of planned visits to asthma care providers, including primary care providers and specialists. All patients who have not used the website within 14 days before their planned visit to an asthma care provider will be sent an automated email reminder, encouraging subjects to use the site or to use a toll-free number to call the study staff if they are having trouble using the website. These email reminders will be repeated 7 days before their next doctor visit and then 3 days before if they have still not used the website. These methods were successful at ensuring a 90% fidelity rate in a pilot RCT of the website 25,27.

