Outpatient asthma care provider visits: The intervention will suggest to some patients, based on rules in the 2007 NAEPP Guidelines, to see an asthma care provider sooner than scheduled (page 345) or to see an asthma specialist (page 288) when none had been seen. It is therefore important to capture these measures of treatment effects. To understand the frequency and timing of primary care and specialist visits for asthma, we will review the Highmark claims database at the end of the 12 month study. The names of providers who are seen will be compared to a database of generalist and specialist physicians that we have used in the past, from SK&A, Inc. Asthma care providers will be determined to be of two types: a) any pulmonologist or allergist seen by the patient, b) any primary care provider seen by the patient who prescribed at least one asthma-related medication during the 12-month study. Visits to these providers will be determined by identifying Highmark claims.

Asthma Self-Management Support Counseling: The 2007 NAEPP Guidelines, as well as previous versions, recommend that physicians should counsel their patients about several aspects of self-management, including recognizing early symptoms of asthma, changing their environment to improve asthma control and creating an asthma action plan 26,29,110. To measure the delivery of this care, we will use standardized measures from the 2003 National Asthma Study, summarized in the National Healthcare Quality Report 9,10. Using this protocol, we will ask specific questions about counseling they received, over the past year, about recognizing early symptoms of asthma, changing their environment to improve asthma control and creating an asthma action plan.

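### A primary care provider's visits count only if that provider prescribed an asthma medicine during the study, so the count depends on an event the intervention aims to change; the visit definition and source also differ elsewhere in the protocol

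*Protocol*

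**What the plan says.** Section 6, Outpatient asthma care provider visits, gives its purpose as: "To understand the frequency and timing of primary care and specialist visits for asthma". It presents these visits as a measure of treatment effect and places them among the mediating variables. Two kinds of provider qualify. Specialists qualify without condition: "any pulmonologist or allergist seen by the patient". Primary care providers qualify only if they meet a prescribing test: "any primary care provider seen by the patient who prescribed at least one asthma-related medication during the 12-month study". The count then follows: "Visits to these providers will be determined by identifying Highmark claims". That last sentence does not restrict the diagnosis or the reason for the visit.

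Two places in section 5 do restrict it. The text says: "Asthma-related claims of hospitalization, outpatient visits, emergency department visits and medications will be examined". The schedule table has a claims row labelled "Outpatient provider visits for asthma".

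The Intervention fidelity paragraph of section 6 defines visits to an asthma care provider differently. It counts any visit to the patient's primary care provider plus "any visits that the patient had with a pulmonary medicine specialist during the study", taken from chart review. There is no prescribing condition, and allergists are not named. The mediation paragraph of section 7 also takes visit timing from chart review.

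**The concern.** A rule that decides which visits count should not itself respond to treatment. Here it can. The intervention condition (IC) prompts patients to ask about controller medicines, and the Controller to reliever ratio paragraph says the intervention is designed to help them receive one. That could make a primary care provider more likely to pass the prescribing test in IC than in the control condition (CC). The intervention also suggests specialist visits. If a specialist takes over all prescribing, the primary care provider could fail the test in IC. Either way, identical visit patterns may be counted differently by arm.

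The visit contrast between arms is at stake, and with it the mediation analysis. That analysis requires an association of treatment with mediator, which the rule can distort. It also requires an association of mediator with outcome. The rule ties the visit count to prescribing by construction, and prescribing is what another listed mediator, the controller-to-reliever ratio, measures.

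**Working it through.** **1. The plan's own figure.** The protocol gives no number for visits. The only related figure is the sample size for the primary outcome, reproduced here for context. With 70% v 55%, two-sided 5% and 80% power, n per arm = [1.960 × √(2 × 0.625 × 0.375) + 0.842 × √(0.70 × 0.30 + 0.55 × 0.45)]² / 0.15² = (1.342 + 0.569)² / 0.0225 ≈ 162.3, so 163. The total is 326, and 326 / 0.80 = 407.5, so 408. Both totals match section 7.

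**2. Size of the prescribing rule alone.** All inputs are assumed. Let A = 2 asthma-related primary care visits per subject-year in both arms, so the true difference is zero. Let q be the share of subjects whose primary care provider prescribed an asthma medicine in the study year, taken as unrelated to the number of visits. Only asthma-related claims are counted.

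False difference (IC − CC) = A × (q_IC − q_CC); ratio = q_IC / q_CC.

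| q_IC | q_CC | Difference | Ratio |
|---|---|---|---|
| 85% | 85% | 0 | 1.00 |
| 90% | 85% | +0.10 | 1.06 |
| 95% | 85% | +0.20 | 1.12 |
| 95% | 75% | +0.40 | 1.27 |

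If specialist takeover dominates, the shares swap and each sign reverses. Restricting to asthma-related claims does not remove this effect.

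**3. Would it be mistaken for an effect?** In a two-sided 5% comparison of mean counts with 163 per arm, a false difference of 0.20 would be significant about 15% of the time if the SD is 2 visits, and 9% if it is 3. A false difference of 0.40 would be significant about 44% and 22% of the time. The SDs are assumed. Claims are requested for all enrolled subjects, so up to 204 per arm could be analysed, which would raise these chances somewhat.

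**4. What hangs on the missing asthma restriction.** If the counting sentence were applied alone, every claim from a qualifying provider would count. Assume O = 1.5 other primary care visits a year in both arms and d extra preventive visits in CC.

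Difference = q_IC × (A + O) − q_CC × (A + O + d).

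| d | 85% v 85% | 95% v 85% |
|---|---|---|
| 0 | 0 | +0.35 |
| 0.25 | −0.21 | +0.14 |
| 0.5 | −0.42 | −0.08 |
| 1.0 | −0.85 | −0.50 |

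Example: 0.95 × 3.5 − 0.85 × 4.0 = 3.325 − 3.400 ≈ −0.08. The result depends entirely on d, which the protocol does not give.

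**5. The definitions side by side.**

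| Place | Primary care visits | Specialists | Asthma restriction | Source |
|---|---|---|---|---|
| Section 6, outpatient visits | Only if provider prescribed in study | Pulmonology, allergy | In the aim, not in the counting sentence | Claims |
| Section 5, text and table | No provider rule | No provider rule | Yes | Claims |
| Section 6, fidelity | Any visit | Pulmonary only | No | Chart review |
| Section 7, mediation | Not defined | Not defined | Not stated | Chart review (timing) |

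The rows cannot all describe the same variable.

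**The case against.** The strongest reply is that the prescribing gap must be small. Entry requires an asthma encounter and at least 3 months of asthma medicines in the prior year. The test is then met by a single asthma medicine of any kind in 12 months, including a reliever or a renewal. Most treating primary care providers should qualify in either arm. This stands as a reason to expect a modest bias. It does not remove the bias, because the entry criterion does not say who prescribed.

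Specialist visits carry no prescribing condition, and the mediation paragraph's own example of a visit mediator is specialist visits. That part is unaffected. The fidelity denominator measures website dose, so a wider scope there may be deliberate; if so, the protocol should say so.

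A reader might infer more: that preventive visits prompted in CC are counted as asthma visits. Section 3 describes CC with the words "active treatment control condition designed to improve the use of adult preventive services (e.g., pap testing), but is unlikely to change asthma care", and the counting sentence has no filter. The documents do not support this. The stated aim of the measure, the claims text and the schedule row all point to visits for asthma. Nor does the protocol say that preventive services become extra visits to the prescribing primary care provider. What remains is an unrestricted sentence that disagrees with its surroundings.

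Counting by asthma diagnosis is not free of treatment influence either. IC patients are prompted to raise asthma at visits, so asthma coding may rise in that arm. This limits the fix and should be acknowledged.

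**Conclusion.** The point holds in a limited form. The primary care rule conditions on prescribing after randomisation, which the intervention aims to change. The visit comparison and the mediation step that uses it can therefore be biased. The size is probably modest: a false 0.10 to 0.40 visits a year for gaps of 5 to 20 points, on an assumed 2 visits. The upper end needs a gap that the entry criterion makes unlikely. The sign is unknown, because prompted prescribing and specialist takeover pull in opposite directions. It would be too strong to say that the comparison is biased, or that non-asthma visits are counted.

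Separately, the definitions and data sources for asthma care visits conflict and need reconciling. Outpatient visits are a mediator and are not among the primary or secondary hypotheses. The Asthma Control Test outcome and N = 408 are untouched.

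**What to change.** - In section 6, Outpatient asthma care provider visits, remove the in-study prescribing condition. Count asthma-related outpatient claims, as section 5 already describes, to any primary care, pulmonary or allergy provider, by the same rule in both arms.
- As a sensitivity analysis, fix primary care provider status from the 2 years of pre-enrolment claims that section 5 already obtains. Do not apply this to specialists, because the measure is meant to capture a specialist seen for the first time.
- Use one provider definition and one data source in the outpatient visit, fidelity and mediation text, or state why the dose denominator differs.

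The cost is a change of definition; no new data are needed. The downside is that asthma visits coded under another diagnosis are missed, and coding may be somewhat more complete in IC. State this as a limitation and do not assume that the loss is equal in both arms.
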